#### *Specific Aim 3: estimate total and mean costs per participant for AR + IVR and UC recipients, and, the incremental cost-effectiveness of AR + IVR at six and twelve months compared to UC from health plan/insurer and societal perspectives*

We hypothesize that AR + IVR is a cost-effective strategy at six and twelve months for smoking cessation compared to UC from societal, health plan/insurer, and individual patient perspectives. Assuming the intervention is effective, we calculate the incremental net cost per additional quit for AR + IVR recipients compared to UC, and incremental costs per quality-adjusted life-years saved (QALYs).

Total intervention costs and costs per participant for AR + IVR and UC are evaluated. All resource costs used to implement and deliver the inpatient and postdischarge follow-up services, counseling programs, medications, and IVR calls are included in the cost calculations. The incremental net cost is calculated per additional quit for AR + IVR participants compared to UC participants, and incremental costs per quality-adjusted life-years saved (QALYs) [34,35]. Program cost analysis (PCA) is used to assess the actual economic, or opportunity, costs incurred to produce the outcome observed from the AR + IVR and UC interventions. The value and the incremental resources required for the intervention for the health system/insurer and societal perspectives are identified. Individual-level cost data are collected to enable variance estimation for the average cost estimates. Total intervention costs and costs per participant for AR + IVR and usual care recipients are estimated.

Abstinence and cost data are used to calculate the incremental net cost per additional quit for AR + IVR participants compared to UC participants. Incremental total costs and cost per participant, by payment source are reported. Incremental cost-effectiveness ratios (ICERs) are measured as: a) incremental intervention costs per incremental quit from health plan/insurer and patient perspectives; b) incremental total costs (intervention plus health care expenditures during follow-up) per incremental quit from health system/insurer and patient perspectives; c) incremental intervention costs per incremental quality-adjusted life-year (QALY) saved from a societal perspective; and d) incremental total costs (intervention plus health-care expenditures during follow-up) per incremental QALY saved from a societal perspective. QALYs for each intervention arm are estimated using life expectancy data and responses from interviewer-administered EQ5D-5L.

#### *Specific Aim 4: evaluate health care utilization at twelve months for AR + AVR and usual care*

We measure health-care utilization for AR + AVR compared to UC by the mean number of combined outpatient and inpatient encounters (visits) per participant during follow-up. This aim is addressed using participant survey responses and medical records (electronically for those receiving care at KPNW and OHSU facilities). For AR + IVR compared to UC, we measure health-care utilization by the mean number of combined outpatient and inpatient encounters (visits) per participant during follow-up. This aim will be addressed using participant survey responses and medical records (electronically for those receiving care at KPNW and OHSU facilities). The functional form of models 1 and 2 for the primary aim will be restated within a Poisson regression model structure and analyzed using SAS PROC GENMOD, specifying a log link function and Poisson distribution.

Health-care utilization data are regularly characterized by nonnormal distributions. While zero values are not expected for visits in the study population, there may be substantial variation in the number of visits completed. Depending on the number of inpatient visits, analysis of the number of inpatient days separately from outpatient visits may be conducted. If the variance is greater than the mean, we will control for the impact of overdispersion by including a term in the model for the unobserved heterogeneity of each i^th^ observation. If data allow separate modeling of inpatient days, the large number of zero stays will require specifying a zero-inflated negative binomial model.

#### *Sensitivity and threshold analyses*

Sensitivity of cost-effectiveness ratios to key parameters: intervention acceptance, intervention costs, abstinence rate, discount rate, pharmacotherapy use and costs, and QALYs saved are measured. Threshold analyses for key parameters are used to identify input levels that alter conclusions. The cost-effectiveness analysis above reflects a deterministic approach using standard univariate and multivariate sensitivity analyses to test the robustness of the results. Based on the results of these analyses, probabilistic sensitivity analyses will be considered, but only if the standard sensitivity tests are unclear or not informative [36-39].

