#### *Power*

A 2:1 ratio of AR + IVR to UC for 900 randomized participants will provide adequate power to detect an eight percentage point difference in thirty-day point prevalence abstinence at six months (our primary outcome), assuming an unbiased method of assigning an outcome to nonrespondents. The unbalanced design requires 864 participants to achieve 80% power, with two-tailed α set at .05, to detect a difference in thirty-day abstinence of eight percentage points between treatment groups. We expect the UC group will achieve a 15% abstinence rate, based on analyses of EMR data (unpublished) for similar populations at each site. An odds ratio of 1.65 for patients with >30 days of follow-up [3] results in a 23% expected abstinence rate for the AR + IVR group. The power calculations were conservative [25-28] and no continuity correction was applied. Rounding up to 900 total participants added an additional measure of conservatism.

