#### *Health-related quality of life*

We obtain patient responses from the EuroQual (EQ5D-5L) [29-31] at baseline and six- and twelve-month follow-up for assessing changes in health-related quality of life for AR + IVR versus UC participants during the study period. Responses are combined with remaining life expectancy data for current and former smokers [32] to estimate differences in expected quality-adjusted life years saved by treatment group.

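### No sampling uncertainty is planned for the cost-effectiveness ratios: probabilistic analysis depends on an undefined, after-the-fact trigger, and reporting after a null result is left unsettled

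*Protocol article*

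**What the plan says.** Specific Aim 3 hypothesises that AR + IVR is cost-effective from the societal, insurer and patient perspectives. Its third paragraph defines four ratios, beginning: "Incremental cost-effectiveness ratios (ICERs) are measured as: a) incremental intervention costs per incremental quit from health plan/insurer and patient perspectives". The others replace intervention cost with total cost, quits with QALYs, or both. No interval or variance method is attached to any of them.

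The section Sensitivity and threshold analyses describes the method: "The cost-effectiveness analysis above reflects a deterministic approach using standard univariate and multivariate sensitivity analyses to test the robustness of the results". It lists the parameters to be varied, among them abstinence rate, intervention costs, discount rate and QALYs saved. It then says that "probabilistic sensitivity analyses will be considered, but only if the standard sensitivity tests are unclear or not informative".

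The data are at participant level. On cost, Aim 3 says: "Individual-level cost data are collected to enable variance estimation for the average cost estimates". The section Health-related quality of life obtains EQ5D-5L responses "at baseline and six- and twelve-month follow-up for assessing changes in health-related quality of life for AR + IVR versus UC participants". Abstinence is the primary outcome.

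On when the ratios are calculated, Aim 3 says two things. Its first paragraph has "Assuming the intervention is effective, we calculate the incremental net cost per additional quit for AR + IVR recipients compared to UC", and the same sentence goes on to cost per QALY. Its second paragraph repeats the calculation without that condition, and its third opens: "Abstinence and cost data are used to calculate the incremental net cost per additional quit for AR + IVR participants compared to UC participants".

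**The concern.** Deterministic sensitivity analysis shows how a ratio moves when chosen inputs are moved. It does not show how far incremental cost and incremental effect, estimated together from 900 people, could differ from their true values by chance. This trial observes both on each participant, so that uncertainty can be estimated directly.

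The trigger for going further has no criterion. Whether sampling uncertainty is examined would be decided by people who have already seen the deterministic ratios.

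The two statements in Aim 3 on effectiveness add a reporting question. If the abstinence result is null, one sentence suggests that no ratio is calculated and the others suggest that it is.

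The economic question is prominent. Economic effects are in the article's title, cost-effectiveness is a stated hypothesis, and the Discussion says that the cost analyses are meant to support the health systems' financial decisions. A point ratio with deterministic ranges could look firmer to those readers than the data allow.

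**Working it through.** **Inputs.** From Power: 15% abstinence in UC, 23% in AR + IVR, two-sided alpha 0.05, 80% power, no continuity correction. From Randomization: 300 AR + IVR and 150 UC at each of two sites, so 600 and 300 in total. The article gives no cost figures.

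**Step 1: reproduce the plan's own figure.** The Power section states: "The unbalanced design requires 864 participants to achieve 80% power, with two-tailed α set at .05". With 2:1 allocation the pooled rate is (0.15 + 2 × 0.23)/3 = 0.2033.
- n(UC) = [1.960 × √(0.2033 × 0.7967 × 1.5) + 0.842 × √(0.15 × 0.85 + 0.23 × 0.77/2)]² / 0.08²
- = [0.966 + 0.391]² / 0.0064, which rounds up to 288.
- Total = 288 × 3 = 864, an exact match, so the inputs are read as intended.

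**Step 2: sampling error of the abstinence difference.**
- SE = √(0.23 × 0.77/600 + 0.15 × 0.85/300) = 0.0268.
- 95% CI = 0.08 ± 1.96 × 0.0268 = 0.0274 to 0.1326, that is, 2.7 to 13.3 percentage points.

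**Step 3: carry it to cost per additional quit.** Let C be the incremental cost per participant, held fixed.
- Point value: C/0.08 = 12.5C.
- Limits: C/0.1326 = 7.5C and C/0.0274 = 36.5C.
- Relative to the point value: 7.5/12.5 = 0.60 and 36.5/12.5 = 2.9, a 4.8-fold range.

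**Step 4: add cost variability, on assumed figures.** Cost distributions are not in the article, so these are illustrations only. Costs were simulated independently of abstinence (400,000 trials), with a coefficient of variation (CV) of 0.5 to 2.

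| Incremental cost (assumed) | CV | Point value and 95% limits, in units of mean UC cost |
|---|---|---|
| equal to mean UC cost | 0.5 | 12.5 (7.4 to 36.3) |
| equal to mean UC cost | 2 | 12.5 (6.1 to 37.7) |
| half of mean UC cost | 0.5 | 6.25 (3.6 to 18.3) |
| half of mean UC cost | 2 | 6.25 (1.9 to 19.9) |

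In the first three rows abstinence dominates. In the last, the lower limit falls to 1.9/6.25 = 0.30 of the point value, so cost variability is not always negligible.

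**Step 5: compare the statements on effectiveness.** Aim 3's first paragraph attaches the assumption to cost per quit and cost per QALY. Its second paragraph, and the opening sentence and ratio definitions of its third, carry no such condition. The word effective is not defined by outcome, time point or test. The text therefore supports both readings.

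**The case against.** Several parts of the case against this point stand, and they limit it.

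- **A reader might infer that the analysis is deterministic only.** It is not: a probabilistic analysis is kept as an option. The fault is that the option is contingent and its trigger undefined.
- **A reader might infer that nothing in the economic analysis carries sampling uncertainty.** Variance estimation is planned for mean costs. What is absent is uncertainty for the ratios and for cost and effect jointly.
- **The 0.60 to 2.9 range amounts to a one-way variation of the abstinence rate, which the plan already lists.** This is fair: an analyst who chose the confidence limits as the range would display that spread. But nothing in the article ties the range to sampling error, so the spread is not assured.
- **A reader might infer that ratios appear only after a significant primary result.** On that reading, with power of 81.7% at 900, about one trial in five with the planned effect would report none. The mean observed difference among the rest would be 8.9 rather than 8.0 points, which flatters cost per quit. The article does not support this reading: it names no test or outcome in that clause, Aim 3 also covers twelve months, and the calculation is stated elsewhere without the condition.
- **There is a sensible motive for the condition.** A ratio is hard to interpret when the difference in quits is near zero or negative. That argues for reporting net benefit, not for leaving the matter open.
- **The QALY ratios draw on external life-expectancy data,** whose uncertainty a participant bootstrap cannot carry. This is correct, and it is why deterministic analysis keeps a place.

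The central point remains. The deterministic default is an explicit choice in the text, not a detail left out of a condensed article.

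**Conclusion.** The point holds in this form: no interval or joint cost-effect uncertainty is planned for any of the four ratios, the route to a probabilistic analysis is undefined and depends on results already seen, and Aim 3 is inconsistent on whether the ratios depend on effectiveness.

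The size is a 4.8-fold range for cost per quit from abstinence sampling alone. It assumes the planned rates, all 900 participants analysed, a normal-approximation interval and fixed incremental cost. The uncertainty once real costs are included cannot be sized from the article.

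This is worth correcting but concerns a secondary aim, and the test of the primary outcome is untouched. Confidence is high on the missing uncertainty analysis. On conditional reporting the text shows only an inconsistency, not an intention to suppress a null result.

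**What to change.** 1. In Sensitivity and threshold analyses, replace the contingent trigger with a prespecified analysis: a non-parametric bootstrap of participants' cost-outcome pairs within arm and site, or a net-benefit regression. Report incremental cost, incremental effect and net benefit with intervals, and an acceptability curve over a stated range of willingness-to-pay values.
2. Keep the deterministic and threshold analyses for inputs not observed in the trial, such as life expectancy and the discount rate.
3. In the first paragraph of Specific Aim 3, delete the opening assumption of effectiveness, and state that the economic results are reported whatever the primary result.

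The cost is a little more programming, with no new data and no change to trial conduct. The downside is that the reported ratios will look less certain than bare point values would.

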### Missing and incomplete data

Nonresponse is defined as when a participant is lost to follow-up or refuses to answer questions about their smoking status. For our primary hypothesis test, we assume participants lost to follow-up are smokers. Depending on actual follow-up rates achieved, the results may be presented using recommended new strategies [40] to deal with missing data. Characteristics associated with nonresponse in smokers are used with SOLAS and SAS programs for implementing multiple imputation procedures. A complete record of subject assignment and attrition will be included in published reports of this trial. For subject attrition, the type of attrition (that is, ‘lost to follow-up’, ‘deceased’, and ‘refused to continue participation’) is monitored. An attempt will be made to identify the causes of missing data. If smokers are more likely than nonsmokers to be lost to follow-up or to be refusals, then nonresponse is ‘nonignorable’ (that is, nonresponse is related to the value of the smoking variable that would have been observed).

A large proportion of the study population will have had a major adverse health event. Thus, the number of patients deceased at follow-up may be higher than is typical in other smoking cessation studies. Patients deceased before follow-up will be excluded from the primary outcome analyses. We will identify the number of deceased patients in the consort table. We may include deceased patients in the economic evaluation because of the high cost of end-of-life care. In the cost-effectiveness analyses, we will evaluate deceased patients as smokers (treatment failures) and assign them a health-related quality of life value of 0. We will also use analytic methods that account for censoring for patients with limited health-care utilization data. For example, for KPNW participants who leave the plan after several months, and for whom we are unable to obtain medical records and expenditures for the entire follow-up period, will have their encounter (visit) and expenditure data for the entire follow-up period annualized based on the proportion of the year for which they were enrolled in the heath plan.

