#### *Health-care utilization and expenditures*

We collect health-care utilization data beginning with the initial hospitalization through 12-month follow-up. Data include: encounters by type (primary care, emergency department, urgent care, hospital admissions); length of hospital stay (initial and subsequent hospitalizations); discharge diagnoses (ICD-9); procedures (CPT-4); pharmacy dispenses and NDC codes; diagnostic-related groups; and medical records data for health-care expenditures (actual costs based on relative-value units and paid claims; retail costs for medications) by source of payment. Data are used to assess differences in utilization and expenditures by treatment group.

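### Scaling plan leavers' encounters and costs by the fraction of the year enrolled, with the window undefined and no person-time term, can inflate Aim 3 and Aim 4 means and misweight short records

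*Protocol article*

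**What the plan says.** The section *Missing and incomplete data* promises: "We will also use analytic methods that account for censoring for patients with limited health-care utilization data". The one method it then describes, given as an example, is "for KPNW participants who leave the plan after several months, and for whom we are unable to obtain medical records" or cost data covering the whole period. The rule for this group reads: "encounter (visit) and expenditure data for the entire follow-up period annualized based on the proportion of the year for which they were enrolled". Nothing is carved out of the scaling.

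The section *Health-care utilization and expenditures* says: "We collect health-care utilization data beginning with the initial hospitalization through 12-month follow-up". The length of the initial stay is among the items it lists.

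The analysed quantities are worded differently. Specific Aim 4 uses the "mean number of combined outpatient and inpatient encounters (visits) per participant during follow-up", modelled in PROC GENMOD "specifying a log link function and Poisson distribution", with a heterogeneity term added if the variance exceeds the mean. No person-time term is mentioned. In Specific Aim 3, ratio (b) is "incremental total costs (intervention plus health care expenditures during follow-up) per incremental quit", and ratio (d) is the same cost per QALY. Ratios (a) and (c) use intervention costs only.

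**The concern.** Annualizing in proportion to time enrolled recovers a full-year total only if use accrues at a constant rate. Two features of this trial make that doubtful. First, every participant enters through a hospital admission, and the data start there. If that one-off stay is in the scaled quantity, it is multiplied along with everything else. Second, if use is heavier in the weeks after discharge, scaling an early segment overstates the year even without the index stay.

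There is also a modelling issue. On the natural reading, a scaled value enters the Poisson model as a full-year count, so three months of observation carry the same weight as twelve.

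At stake are mean visits and mean costs by arm and, under conditions set out below, the Aim 4 comparison and total-cost ratios (b) and (d). The primary abstinence outcome is not touched.

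**Working it through.** The plan states no figure on this point, so there is none to reproduce.

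**Inputs.** From the protocol: 450 participants per site, so KPNW is half of 900. Not given, and therefore assumed: fraction of the year observed f = 0.25, 0.50 or 0.75; share of KPNW participants leaving p = 5% to 20%; index-stay cost 10,000 to 30,000 units; all use and cost profiles below.

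**1. Index stay included.** Let the index quantity be I and the constant post-discharge yearly total be r. The annualized value is (I + r·f)/f = I/f + r, against the correct I + r. The excess per leaver is I·(1/f − 1).
- The index stay is counted 4, 2 or 1.33 times at f = 0.25, 0.50 or 0.75, which is 3, 1 or 0.33 spurious admissions per leaver.
- The excess in the KPNW mean is p·(1/f − 1) encounters: 0.15 to 0.60 at f = 0.25, 0.05 to 0.20 at f = 0.50, and 0.02 to 0.07 at f = 0.75. Trial-wide it is about half that.

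**2. Index stay excluded.** With a constant rate, r·f/f = r and there is no bias. With an assumed front-loaded profile of 8 per year plus an extra 24 per year decaying with a two-month time constant, cumulative use at time t (in years) is 8t + 4·(1 − exp(−6t)). The true year is 11.99.
- f = 0.25: annualized 20.43, ratio 1.70.
- f = 0.50: annualized 15.60, ratio 1.30.
- f = 0.75: annualized 13.27, ratio 1.11.

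**3. Difference between arms, KPNW, index stay included.** Assume post-discharge rates of 9 (AR + IVR) and 10 (UC) per year and f = 0.5. True means are 10 and 11: difference −1.0, ratio 0.909.
- 10% leave in each arm: 0.9×10 + 0.1×11 = 10.1 and 0.9×11 + 0.1×12 = 11.1. The difference is still −1.0 and the ratio is 0.910.
- 15% leave AR + IVR and 5% leave UC: 0.85×10 + 0.15×11 = 10.15 and 0.95×11 + 0.05×12 = 11.05. The difference is −0.9 and the ratio 0.919.
- The bias in incremental cost per KPNW participant is (difference in leaving)·(1/f − 1)·(index cost). For 20,000 and a 5-point difference this is 1,000 at f = 0.5 and 3,000 at f = 0.25. Over 10,000 to 30,000 the range is 500 to 4,500. With equal leaving it is 0.

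**4. Use that the intervention brings forward.** AR + IVR patients are helped to enroll and have medication orders initiated before discharge, and the IVR calls end at about day 49. Pharmacy dispenses are part of the utilization data. If incremental use is complete before a patient leaves, the KPNW arm difference in that use is overstated by p·(1/f − 1) even with equal leaving. At p = 10% this is 10% for f = 0.5 and 30% for f = 0.25.

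**5. Variance.** If the observed count Y is Poisson with mean λf, the scaled Y/f has variance λf/f² = λ/f: 4λ, 2λ or 1.33λ, where a plain Poisson model assumes λ. If 10% of KPNW participants (5% of the trial) leave at f = 0.25, the average variance is 0.95 + 0.05×4 = 1.15 times that assumed, so standard errors are about 7% too small. At f = 0.5 it is 0.95 + 0.05×2 = 1.05, or about 2%.

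**6. What an offset does.** Take the profile in step 2 with 10% leaving at f = 0.25. Annualizing gives a mean of 0.9×11.99 + 0.1×20.43 = 12.83, which is 7% high. An offset gives total events over total time, (0.9×11.99 + 0.1×5.11)/(0.9 + 0.1×0.25) = 12.22, which is 2% high.

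**The case against.** A reader might infer that the plan definitely multiplies the index admission. The documents do not establish this. Starting collection at admission does not define the analysis window. The scaling sentence and both aims refer to follow-up, and Aim 4 expects many zero inpatient stays if inpatient days are modelled separately. That would be impossible if the index stay counted, since everyone has one. This stands for inpatient days. It does not settle combined encounters or expenditures, for which no passage excludes the index stay.

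Nor do the documents say that use is heaviest just after discharge. That is an assumption here, and under a flat rate with the index stay excluded the rule is unbiased.

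It is also fair that ratios (b) and (d) depend on differences between arms, where the index excess cancels under equal leaving, and that the documents give no reason to expect unequal leaving. Step 4 of the working is the exception, and it depends on how much use really moves early.

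A claim that Aim 4 standard errors are simply too small would ignore the planned overdispersion term. That term absorbs part of the extra variance on average. It does not restore the right weight to short records, and a three-month zero still becomes a full-year zero.

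Finally, annualization is offered as an example, and an article may leave detail to a fuller plan. But this is a concrete rule stated for a named group, not a silence.

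**Conclusion.** The point holds in conditional form. The scaling rule exempts nothing and the window it applies to is not defined. If the index stay is inside, arm means are inflated: each leaver's index stay counts 1.33 to 4 times over the assumed range of f. If it is outside, the rule is correct only under constant post-discharge use; the assumed front-loaded profile overstates leavers by 1.11 to 1.70 times.

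Bias in arm differences and in ratios (b) and (d) is possible, not certain. It needs leaving or its timing to differ by arm, or use to be shifted early by the intervention. It would be wrong to conclude that Aims 3 and 4 as a whole are biased: ratios (a) and (c) use intervention costs only, and only KPNW leavers without obtainable records are affected. Their number is not given, so the net size cannot be stated. A reader might also suppose that patients who die are scaled up in the same way, but the section treats deaths separately and says no such thing.

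The weighting and variance fault is real if the scaled value is analysed as a full-year count, which is the natural reading. Under the assumptions shown, it is modest for the trial as a whole.

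**What to change.** 1. State that the utilization and cost window starts at discharge from the index stay. Alternatively, include the index stay but report it separately and never scale it.
2. For Aim 4, drop annualization. Model the observed post-index count with log(person-time observed) as an offset in the Poisson or negative binomial model. An offset alone still assumes a common rate over time, so if use falls after discharge, split follow-up into intervals with an interval term.
3. For Aim 3 total costs, ratios (b) and (d), use a censoring-adjusted estimator of the 12-month mean, for example inverse-probability-of-censoring weighting by interval. Keep annualization at most as a sensitivity analysis.
4. Report the number of leavers and their time enrolled, by arm.

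The cost is some analysis-plan wording and modest extra programming. The enrollment dates are already needed for the current rule, so no new data are required.
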